## Management of Infusion-Related Reactions

| NCI-CTCAE Grade                                                                                                                                                                                                                                                                                                                                                    | Treatment Modification for Avelumab                                                                                                                                                                                   |
|--------------------------------------------------------------------------------------------------------------------------------------------------------------------------------------------------------------------------------------------------------------------------------------------------------------------------------------------------------------------|-----------------------------------------------------------------------------------------------------------------------------------------------------------------------------------------------------------------------|
| Grade 1 - mild
Mild transient reaction; infusion interruption not indicated; intervention not indicated                                                                                                                                                                                                                                                  | Decrease the Avelumab infusion rate by 50% and monitor closely for any worsening                                                                                                                                      |
| Grade 2 - moderate
Therapy or infusion interruption indicated but responds promptly to symptomatic treatment (for example , antihistamines, NSAIDs, narcotics, Iv fluids) ; prophylactic medications indicated for ≤ 24 h                                                                                                                                | Temporarily discontinue Avelumab infusion
Resume infusion at 50% of previous rate once infusion-related reaction has resolved or decreased to at least Grade 1 in severity , and monitor closely for any worsening |
| Grade 3 or Grade 4 - severe or life-threatening
Grade 3: Prolonged (for example, not rapidly responsive to symptomatic medication and/or brief interruption of infusion); recurrence of symptoms following initial improvement; hospitalization indicated for clinical sequelae
Grade 4: Life-threatening consequences; urgent intervention indicated | Stop the Avelumab infusion immediately and disconnect infusion tubing from the subject
Subjects have to be withdrawn immediately from Avelumab treatment and must not receive any further Avelumab treatment       |

### 7.7. PACKAGING AND LABELING

The following information will appear on the labels:

- Name of the Sponsor.
- Study number/Patient number.
- Dosage and route of administration.
- Quantity or contents of container.
- Batch number/packaging number.
- Expiration date and storage conditions.
- Local legal information, as appropriate.

### 7.8. SUPPLIES AND DRUG ACCOUNTABILITY

Regorafenib and Avelumab will be supplied to investigators.

For ordering study drugs, please confer process of this study and pharmaceutical procedure.

Proper drug accountability will be done by the clinical trial monitor. Each study site will keep records to allow a comparison of quantities of drug received and used at each site. The Investigator at each study site will be the person ultimately responsible for drug accountability at the site.

All unused drug supplied by the Sponsor will be properly destroyed at the study site, at the end of the study. The documentation of this procedure must be provided to the clinical trial monitor.

### 7.9. TREATMENT COMPLIANCE

The Investigator is responsible for supervising compliance with the instructions described in this study protocol.

## 8. STUDY EVALUATIONS

Study evaluations aim to assess:

- Diagnosis
- Efficacy
- Safety

## 8.1. CENTRAL REVIEW FOR DIAGNOSIS, IMMUNE SIGNATURE AND PROGRESSIVE DISEASE

### 8.1.1. *Diagnosis*

#### 8.1.1.1. DIAGNOSIS OF GIST (COHORT B) AND STS (COHORTS E (STS) AND I (SOLID TUMORS STS-TLS+))

If diagnosis was not confirmed by the RRePS Network, pathological central review will be performed to confirm histological diagnosis of sarcoma by [name] and collaborators, Department of Pathology, Institut Bergonié, Bordeaux, France. The reviewer will assess pathological diagnosis; document the results on the 'Pathological request form' response completed and sign this form.

Every discrepancy will be discussed between referral investigator, Pr [name] or collaborators and the Sponsor, until a final decision is reached. Patients with diagnosis different from GIST or STS will be considered ineligible and will not be included in the study.

#### 8.1.1.2. PATHOLOGICAL SPECIMEN SAMPLING NECESSARY FOR CENTRAL REVIEW

For a gross description and diagnostic information concerning pathological specimens, reference to "Recommendations for reporting soft tissue sarcomas" is strongly advised (Recommendations, 1999). Available tumor samples obtained at diagnosis or at relapse, as unstained slides (10), and/or preferable paraffin-embedded tumor blocks (one or two) are mandatory for central review.

#### 8.1.1.3. PATHOLOGICAL PROCESS SCHEDULE AND IMPLEMENTATION (NOT APPLICABLE IF DIAGNOSIS REVIEWED IN RRePS NETWORK)

Each site will send to Institut Bergonié within 7 days after the signature of informed consent:

- Pathology request form completed
- 10 unstained slides and/or preferable FFPE (Formalin-Fixed Paraffin-Embedded) block of specimen tumor sampling, obtained anytime during disease development
- Initial pathology report with patient code and date of birth (including macroscopic description) and pathology report of molecular biology if any.

All material must be sent to:

### 8.1.2. *Immune signature - Central review before inclusion*

#### 8.1.2.1. IMMUNE SIGNATURE FOR SOLID TUMOR (TLS) (COHORT I) AND COLORECTAL CANCER (COHORT A')

Centralized analysis for immune signature will be performed to determine the status of mature tertiary lymphoid structures (TLS) (Cohort I) and the level of tumor-associated macrophages infiltrate (Cohort A') at inclusion time.

This will be performed by centrally reviewing, except if already confirmed by Biopathological platform at Bergonié Institute (cf §6.2.1).

#### 8.1.2.2. PATHOLOGICAL SPECIMEN SAMPLING NECESSARY FOR CENTRAL REVIEW

Archived or newly obtained FFPE (Formalin-Fixed Paraffin-Embedded) block are mandatory for central review.

#### 8.1.2.3. PATHOLOGICAL PROCESS SCHEDULE AND IMPLEMENTATION

Each site will send to Institut Bergonié within 7 days after the signature of informed consent:

- Pathology request form completed (specific Transfert Form)
- Archived or newly obtained FFPE (Formalin-Fixed Paraffin-Embedded) block, in order to assess the presence of mature TLS in cohort I and the level of tumor-associated macrophages infiltrate in cohort A'

All material must be sent to:

### **8.1.3. Diagnosis of progressive disease – Central review before inclusion – cohorts E (STS), F (RR-DTC) and I (Solid tumors-TLS+)**

#### **8.1.3.1. CENTRALIZED RADIOLOGICAL REVIEW**

Centralized radiological review will be performed to confirm progressive disease status at inclusion time. This will be performed by centrally reviewing:

- For Cohorts E (STS): two CT scans or MRI obtained prior to inclusion (obtained at an interval less than 6 months in the period of 12 months prior to inclusion).
- For Cohort F (RR-DTC): two CT scans or MRI obtained prior to inclusion (obtained at an interval less than 12 months prior to inclusion).
- For Cohorts I (Solid tumors-TLS+): two CT scans or MRI obtained prior to inclusion (obtained at an interval less than 6 months in the period of 12 months prior to inclusion).

#### **8.1.3.2. GENERAL PROCEDURE**

Review process will be centralized at Institut Bergonié and will be performed by one radiologist expert. The results of the centralized review will be used for the diagnosis for progressive disease.

#### **8.1.3.3. REVIEW PROCESS SCHEDULE AND PRACTICAL IMPLEMENTATION**

With regards to inclusion scan, the progressive disease status at baseline must be confirmed by central review. Within 7 days after the signature of informed consent, each site will send two-imaging CD as described in a specific SOP given by the Sponsor.

## **8.2. EFFICACY – FOR PATIENTS INCLUDED IN PHASE II TRIALS ONLY**

The antitumor activity of Regorafenib given in association with Avelumab will be evaluated in terms of Objective response rate (ORR) under treatment, 6-month Non-progression rate (NPR), best overall response, 1-year Progression-free survival (PFS), 1-year Overall survival (OS). Objective response, Non-progression and best objective response are defined as per the Response Evaluation Criteria in Solid Tumors (RECIST v1.1).

### **8.2.1. Assessing Objective Tumor Response (RECIST v1.1)**

- A comprehensive workup will be performed at baseline, and every 8 weeks.
- Whenever response criteria are met, the appropriate imaging tests should be repeated at least four weeks later in order to confirm the response.
- The same method will be used to evaluate each identified lesion both at baseline and throughout the study.
- Treatment will be administered as long as no disease progression or unacceptable toxicity is found, or as long as no other reasons for treatment discontinuation are met.
- Assessment of efficacy will be essentially based on a set of measurable lesions identified at baseline as target lesions and followed until disease progression and following the RECIST v1.1 criteria (Eisenhauer, 2009).

### **8.2.2. Centralized Radiological Review (Institut Bergonié)**

#### **8.2.2.1. GENERAL PROCEDURE**

Centralized radiological review will be performed to confirm disease status under treatment in comparison with baseline, Week#8, Week #16, Week#24 and every eight weeks thereafter. For patients included in the reference center, CT scan will be initially read by a radiologist who differs from the expert. Review process will be centralized at Institut Bergonié and will be performed by a radiologist expert in solid and digestive tumors.

In case of discordance between the local radiologist and the expert reviewer, the judgment provided by the expert reviewer will be retained to continue or stop the treatment: treatment must be continued until central review response is available.

#### **8.2.2.2. REVIEW PROCESS SCHEDULE**

All tumor evaluations will be sent as soon as there were available. Patient's information must be recorded on a provided imaging CD.

#### **8.2.2.3. PRACTICAL IMPLEMENTATION**

For each shipment, each media should be accompanied by the Radiological Forms provided by the sponsor.

All CDs must be sent to the coordinating clinical research assistant.

### 8.3. SAFETY

Patients will be evaluable for safety if they have received at least one treatment administration. Safety will be evaluated using clinical examinations, which will comprise vital signs analysis, clinical assessment of AEs, changes in laboratory parameters (hematological and biochemical, including liver function tests) and any other analyses that may be considered necessary. Safety profile will be continuously followed during treatment up to 90 days after the last treatment administration or until the start of a new antitumor therapy, whichever occurs first. All AEs will be classified according to the NCI-CTCAE, version 5.0.

## 9. STUDY ENDPOINTS

### 9.1. PHASE I TRIAL

#### 9.1.1. Primary endpoint

- Primary objective of the phase I trial is to establish the recommended phase II dose (RP2D), the maximum tolerated dose (MTD) evaluated on the first cycle (D1 to D28), the safety profile, and the dose limiting toxicities (DLT) of Regorafenib when prescribed in association with Avelumab (no dose escalation for Avelumab) in patients treated for advanced digestive solid tumors.
- Toxicities will be graded using the common toxicity criteria from the NC-CTCAE v5.0.
- Incidence rate of DLT at each dose level on cycle 1 will be reported.
- Dose limiting toxicities are defined as follows:

**Dose-limiting toxicity (DLT)** is defined as an adverse event or laboratory abnormality that fulfills all the criteria below:

- Begins on the first 28 days of treatment
- Is considered to be at least possibly related to the study treatment
- Meets one of the criteria below:
  - Hematotoxicity:
    - Persistent grade 4 neutropenia lasting  $\geq 7$  days;
    - When a neutrophil count of  $< 1000/\text{mm}^3$  and fever of  $\geq 38.0^\circ\text{C}$  is observed for  $> 2$  days;
    - Grade 4 thrombopenia or thrombopenia associated with a hemorrhage requiring platelet transfusion.
    - Grade 3 thrombocytopenia with bleeding.
  - Non-hematotoxicity:
    - $\geq$ Grade 3 non-hematotoxicities are considered as DLTs with the following specifications:
    - $\geq$ Grade 3 diarrhea, nausea, vomiting, and loss of appetite for  $\geq 5$  consecutive days (despite supportive therapy);
    - $\geq$ Grade 3 electrolyte imbalance for  $\geq 7$  consecutive days (despite supportive therapy);
    - Grade 3 dermatologic toxicity (HFSR and non-life threatening events) for  $\geq 7$  consecutive days;
    - Grade 4 dermatologic toxicity of any duration;
    - ALT/AST increases  $5-8 \times \text{ULN}$  with concomitant bilirubin increase  $< 2 \times \text{ULN}$  not resolving to  $< 5 \times \text{ULN}$  within 7 days
    - ALT/AST increases  $5-8 \times \text{ULN}$  with concomitant bilirubin increase  $> 2 \times \text{ULN}$
    - ALT/AST increases  $> 8 \times \text{ULN}$  regardless of concomitant bilirubin increase
    - Bilirubin increase  $> 3 \times \text{ULN}$  not resolving to baseline within 7 days
    - $\geq$ Grade 3 immune-related adverse events lasting for  $\geq 8$  consecutive days despite steroid therapy.

In addition, the following will be considered as DLT:

- Any other study drug related AE considered significant enough to be qualified as DLT in the opinion of the investigators after discussion with the sponsor
- Any drug-related AE leading to Regorafenib or Avelumab relative dose intensity lower or equal to 75% over the first treatment cycle.

### **9.1.2.Secondary endpoints**

- Preliminary signs of antitumor activity in terms of:
  - Best overall response is defined as the best response recorded from the start of the study treatment until the end of treatment taking into account any requirement for confirmation as per RECIST v1.1 criteria (appendix 3). Following RECIST v1.1 recommendations:
    - The best overall response is determined once all the data for the patient is known.
    - Claimed responses will have to be confirmed at least 4 weeks later to ensure responses identified are not the result of measurement errors.
  - Objective response rate (ORR) is defined as the proportion of patients with complete response or partial response according to RECIST v1.1 criteria (appendix 3). ORR under treatment and 6-month ORR will be reported. ORR under treatment is recorded from study treatment initiation until the end of treatment. Following RECIST v1.1 recommendations:
    - ORR under treatment is determined once all the data for the patient is known.
    - Claimed responses will have to be confirmed at least 4 weeks later to ensure responses identified are not the result of measurement errors.
  - Progression-free rate (PFR) is defined as the proportion of patients with complete response, partial response or stable disease more than 24 weeks as defined as per RECIST v1.1 criteria (appendix 3). 6-month PFR will be reported. Following RECIST v1.1 recommendations, claimed responses will have to be confirmed at least 4 weeks later to ensure responses identified are not the result of measurement errors.
  - Growth modulation index (GMI): GMI will be defined for each patient as the ratio of its PFS on Regorafenib + Avelumab treatment to its PFS on the previous line of therapy. This method accounts for inter-patient variability, the patient serving as his/her own control and implies by the natural history of the disease that the PFS tends to become shorter in successive lines of therapy. It is thought that an anti-cancer agent should be considered effective if the GMI is greater than 1.3
  - Progression-free survival (PFS) is defined as the time from study treatment initiation to the first occurrence of disease progression or death (of any cause), whichever occurs first. 1-year PFS rate and median PFS will be reported.
  - Overall Survival (OS) is defined as the time from study treatment initiation to death (of any cause). 1-year OS rate and median OS will be reported.
- PK measurements expressed as AUC, half-life and concentration peak for Regorafenib
- Pharmacodynamic activity: Predictive biomarkers analysis and pharmacodynamic (PD)/mechanism of action (MOA) in blood (levels of angiogenic and immunologic biomarkers in blood at baseline and different study time points), potentially including but not limited to:
  - Serum/plasma cytokines levels (ELISA)
  - Treg, CD4+, CD8+ and DR lymphocytes subpopulations (flow cytometry)
  - Archived tumor tissue will be collected for assessment of tumor VEGFR, PDGFR, HIF1alpha expression and lymphocytes, TAM and MDSC tumor infiltrates (IHC)
  - In addition, for all patients, optional biopsy at baseline and after 4 weeks of treatment will be proposed for mechanisms of action documentation: tumor VEGFR, PDGFR, HIF1alpha expression as well as PD-L1/PD1, lymphocytes, TAM, MDSC tumor infiltrates (IHC) and mutational status.

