| Serum pregnancy test (if indicated)                     | X             | X                           |                 |     |                  | D1                          |                 |     |                  | D1              | D1             |                            |
| PK d – phase I                               |               |                             |                 | D15 |                  | D1                          |                 | D15 |                  |                 |                |                            |
| Biomarkers i                                 |               | D1                          |                 |     |                  | D1                          |                 |     |                  | D1 e | D f |                            |
| Stool sample – phase II (optional) j         |               | D1                          |                 |     |                  |                             |                 |     |                  |                 |                |                            |
| Tumor biopsy (optional)                                 | X             |                             |                 |     |                  | D1                          |                 |     |                  |                 |                |                            |

a: differential WBC, haemoglobin, platelets (During treatment : D1, D8, D15 and D22 of cycle 1 and 2, and repeat before each Avelumab injection (ie. Day 1 and Day 15), at discontinuation visit and safety follow-up visit), aPTT, PT, INR (During treatment : D1, D15 of cycle 1 and 2, then D1 of each subsequent cycle, at discontinuation visit and safety follow-up visit)  
b: albumin, alkaline phosphatase, total bilirubin, urea, calcium, chloride, creatinine, creatinine clearance, glucose, LDH, phosphorus, potassium, total protein, SGOT [AST], SGPT [ALT], GGT, sodium, CPK, lipase, amylase (Screening, C1D1 and D15, C2D1 and D15, then D1 of each subsequent cycle, at discontinuation visit and safety follow-up visit)  
c: blood, glucose, protein, gravity (dipstick)  
d: all blood samples will be collected on pre-dose (1 point)  
e: D1C4, D1C6  
f: at progression  
g: only hepatic assessment (AST, ALT, alkaline phosphatase and GGT)  

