**Recommended phase II dose (RP2D):** will be identified by the steering committee based on the MTD, additional safety data (all cycles), PK data and PD data. Data from all cycles will be used to define the dose level to be recommended for further investigations in phase II

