### 3.2.2. Treatment scheme

Regorafenib will be taken orally once daily for three weeks on/one week off, as appropriate for assigned dose level.

Avelumab will be administered intravenously, at fixed doses of 10 mg/kg, every two weeks, starting on Cycle 1 Day 15.

A treatment cycle consists of 4 weeks. Treatment may continue until disease progression or study discontinuation (withdrawal of consent, intercurrent illness, unacceptable adverse event or any other changes unacceptable for further treatment, etc.).

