## 17. PHARMACOKINETIC, AND ANCILLARY STUDIES

### 17.1. PHARMACOKINETIC STUDY

#### 17.1.1. Collection of available specimens

Pharmacokinetic of Regorafenib and Avelumab in blood will be assessed on Day 15 of cycle 1, Day 1 and Day 15 of cycle 2, in patients treated in the phase I. The main objective of the pharmacokinetic study is to assess the impact of Avelumab on the PK of Regorafenib. PK through values of Regorafenib and Avelumab will be monitored at selected timepoints: at initial administration (C1D15) and after repeated dosing, at the higher theoretical point (C2D15).

For all patients included in the phase I trial, blood samples will be collected at predefined time points as detailed in table below :

Before the perfusion:

| Before the perfusion | H-30 min |
|-----------------------------|-----------------|
| C1D15                       | X               |
| C2D1                        | X               |
| C2D15                       | X               |

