#### 17.1.2. PK analysis

Metabolites concentration of regorafenib (M-2 and M-5) will be monitored.

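### The phase I PK endpoint names AUC, half-life and peak of regorafenib, but the sampling plan collects one pre-infusion sample per visit and supports trough concentrations only.

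*Protocol*

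**What the plan says.** Section 9.1.2 lists, among the phase I secondary endpoints, "PK measurements expressed as AUC, half-life and concentration peak for Regorafenib". The synopsis repeats the same three parameters under Endpoints.

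Sampling is described in two places. In the synopsis schedule of assessments, the phase I PK row marks C1D15, C2D1 and C2D15, and footnote d reads "all blood samples will be collected on pre-dose (1 point". Section 17.1.1 says PK "will be assessed on Day 15 of cycle 1, Day 1 and Day 15 of cycle 2", and its table has a single column, H-30 min before the infusion, for the three visits. It names the quantity: "PK through values of Regorafenib and Avelumab will be monitored at selected timepoints" (evidently trough). It also states the purpose: "The main objective of the pharmacokinetic study is to assess the impact of Avelumab on the PK of Regorafenib".

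Section 17.1.2, on PK analysis, says only: "Metabolites concentration of regorafenib (M-2 and M-5) will be monitored". It names no model-based or sparse-sampling method.

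Two other passages matter. Under section 3.2.2, "Regorafenib will be taken orally once daily for three weeks on/one week off", while avelumab starts on C1D15. Under section 3.2.1, the RP2D is chosen "based on the MTD, additional safety data (all cycles), PK data and PD data".

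**The concern.** The endpoint and the sampling plan describe different quantities. AUC, peak and half-life summarise a concentration-time profile; the plan yields one trough per visit. A statistical analysis plan can choose a method, but it cannot supply samples that were never scheduled.

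If the wording stands, either the endpoint goes unreported, or values of AUC, peak and half-life appear that rest largely on outside assumptions while looking like measurements. PK is also a named input to the RP2D, so readers should know what kind of PK information the trial can provide.

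**Working it through.** **Inputs from the protocol.** Three PK visits (17.1.1); one pre-dose sample per visit (schedule, footnote d); once-daily dosing, D1 to D21 of a 28-day cycle (7.3); avelumab on C1D15, then D1 and D15 of later cycles (7.3); 6 to 12 phase I patients (synopsis). The protocol gives no half-life or absorption rate for regorafenib, so those below are assumptions, shown as ranges.

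**Step 1: count the samples.** 3 visits × 1 sample = 3 per patient. Post-dose samples: 0. Samples in any one dosing interval: at most 1.

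**Step 2: does a trough determine AUC or peak?** Assume a one-compartment oral model at steady state, with τ = 24 h and k = ln 2 / t½:

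C(t) ∝ e^(−kt)/(1 − e^(−kτ)) − e^(−ka·t)/(1 − e^(−ka·τ))

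In the same units AUC(0–24) = 1/k − 1/ka, and the trough is C(24).

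- t½ 12 h, ka 1.5 per h: AUC = 17.31 − 0.67 = 16.65; trough = 0.25/0.75 = 0.333; ratio 49.9.
- t½ 60 h, ka 0.2 per h: AUC = 86.56 − 5.00 = 81.56; trough = 3.130 − 0.008 = 3.121; ratio 26.1.

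| t½ (h) | ka (per h) | AUC/trough | Peak/trough |
|---|---|---|---|
| 12 | 0.2 | 37.9 | 1.97 |
| 12 | 1.5 | 49.9 | 3.41 |
| 24 | 0.5 | 32.6 | 1.65 |
| 60 | 0.2 | 26.1 | 1.14 |
| 60 | 1.5 | 27.4 | 1.27 |

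For one and the same observed trough, AUC varies by 49.9/26.1 = 1.9-fold and peak by 3.41/1.14 = 3.0-fold. The trough fixes neither.

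**Step 3: half-life.** No dosing interval has two samples, so no slope can be fitted within one. The only pair carrying elimination information is C1D15 and C2D1. From D22 (24 h after the last tablet) to C2D1 is 7 × 24 = 168 h, and the fraction of trough remaining is 2^(−168/t½):

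| t½ (h) | C2D1 as share of trough |
|---|---|
| 12 | 2^(−14) = 0.006% |
| 24 | 2^(−7) = 0.8% |
| 36 | 3.9% |
| 60 | 2^(−2.8) = 14% |

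A two-point estimate would need the D15 trough to stand for D22, uninterrupted dosing in between, single-phase decay and a quantifiable C2D1 level. The protocol states none of these. Section 7.5.3.2 says regorafenib may undergo enterohepatic circulation, which makes single-phase decay doubtful. The first avelumab infusion also falls just after the C1D15 sample, so taking the trough as unchanged to D22 presupposes the answer to the stated aim.

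**Step 4: what the samples do support.** C1D15 precedes the first avelumab infusion. C2D15 falls on the same regorafenib day after two infusions (C1D15 and C2D1). This is a like-for-like trough contrast, one pair per patient. C2D1 follows the off week, so it is not an on-treatment regorafenib trough; for avelumab it is a valid trough, two weeks after the first infusion.

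**The case against.** A reader might infer that none of the three parameters can be estimated at all. That goes too far: a crude washout half-life from C1D15 to C2D1 is conceivable under the assumptions in Step 3, and a model borrowing external population-PK information could return values of all three. The phase I analysis plan, which is not at hand, might contain such a model. What remains is that the scheduled samples alone give neither AUC nor peak, and standard analysis gives no half-life.

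A reader might also infer that the secondary objective cannot be met. The documents do not support that. Section 2.2.1 asks only for a description of regorafenib PK, and 17.1.1 asks about the impact of avelumab. Troughs serve both in a limited way. It is the endpoint's list of parameters that fails.

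The practical weight is modest: this is one descriptive secondary endpoint in a small dose-escalation part. Section 7.3 already gives the phase II dose as defined in phase I, so the edit may be retrospective. That limits what the correction achieves, but the mismatch remains.

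**Conclusion.** The point holds as an internal contradiction between the endpoint (9.1.2, synopsis) and the sampling plan (schedule footnote d, 17.1.1). AUC and peak are unobtainable from the scheduled samples alone, and half-life is unobtainable by standard analysis. This follows from the sample count and needs no model; the 1.9-fold and 3-fold ranges illustrate its size and depend on the assumed one-compartment model and parameter ranges.

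It would be wrong to conclude that the RP2D is unsound. Section 3.2.1 bases it on the MTD, safety and PD data as well as PK, and nothing in the protocol shows that it turned on an AUC or a peak.

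The usable contrast, C2D15 against C1D15, is limited to at most 6 to 12 pairs. The number falls wherever regorafenib was reduced or interrupted, which section 7.6.2 permits, because the ratio would then mix a dose change with any avelumab effect.

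**What to change.** - In 9.1.2 and the synopsis, replace AUC, half-life and peak with pre-dose concentrations of regorafenib, M-2 and M-5, and of avelumab, which 17.1.1 already measures.
- In 17.1, name the within-patient C2D15/C1D15 ratio as the measure of avelumab's effect on regorafenib. Restrict it to, or flag, patients whose regorafenib dose was unchanged and uninterrupted before both samples. The choice of interval can stay in the analysis plan.
- Report regorafenib at C2D1 separately as a value after the off week, and keep C2D1 as an avelumab trough.
- Record the time of the last regorafenib intake for each sample. H-30 min is timed to the infusion, footnote d does not say which drug its pre-dose refers to, and 17.1.1 does not tie the sample to the tablet. If the medication diary required by 7.3 holds clock times, they can be taken from there.

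The cost is wording, plus the intake time where it is not already recorded; no new samples are needed. The PK claim becomes more modest. If phase I data are already collected, document the change as a correction with its reason, so that it is not read as an endpoint dropped after the results were seen.
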